## Abstract

**Background:**

This study is designed to evaluate the main hypothesis that nafamostat mesilate with standard therapy improves the severity and mortality rate in patients with COVID-19 pneumonia.

**Methods:**

We conduct a randomized, open type, multi-institute/center, 2-group clinical trial with COVID-19 pneumonia patients in Korea. Eighty four patients with COVID-19 pneumonia are randomly assigned to intervention group or control group. Patients in intervention group receive the standard therapy with a dose of 0.1 to 0.2 mg/kg/h (2.4 to 4.8 mg/kg/day) of nafamostat mesilate. Patients in control group receive the standard therapy such as lopinavir/ritonavir, hydroxychloroquine, oxygen therapy, non-invasive and invasive ventilator, antibiotic therapy, renal-replacement therapy, and extracorporeal membrane oxygenation (ECMO). The primary outcome is proportion of patients with clinical improvement as defined by live discharge from hospital or a decline of 2 categories on the seven-category ordinal scale of clinical status, as well as secondary outcome comprised change in National Early Warning Score, duration of hospitalization, incidence of new-non-invasive ventilation or high flow oxygen use or ventilator, mortality at day 28, viral load change, and adverse events.

**Discussion:**

Our study contributes to the establishment of therapeutic strategy in COVID-19 pneumonia by evaluating the therapeutic effect and safety of nafamostat mesilate.

**Trial registration:**

ClinicalTrials.gov NCT04418128. Registered on 5 June 2020.

## Introduction

### Background and rationale {6a}

The COVID-19 epidemic expanded to the whole world since it started from the Wuhan area in China in December 2019. The Republic of Korea experiences a sharp increase in the patient since 24 February 2020. In an analysis of more than 70,000 patients in China, about 15% of them cause severe pneumonia, 5% require treatment in the intensive care unit, and a half of them die of the disease.

There are no proven therapeutics for COVID-19 patients yet. Currently, the treatment with lopinavir/ritonavir, hydroxychloroquine, etc., did not show apparent effect [1], and there are no other drugs that can be applied to patients who get worse even with those drugs or who are severe.

There are research reports that defective innate immunity and accelerated activation of the complement cascade, caused by the SARS-CoV-2, induce rapidly progressing pneumonitis [1, 2].

SARS-CoV-2 is a single-stranded RNA-enveloped virus and contains four structural proteins (S, E, M, and N) [3]. The spike (S) protein of coronaviruses facilitates viral entry into target cells [4]. Entry requires S protein priming by cellular proteases; SARS-S employs the cellular serine protease TMPRSS2 for S protein priming [4]. The previous study reported that, in MERS-CoV, another type of coronavirus, nafamostat blocks TMPRSS2 activity, thereby suppressing membrane fusion between the virus and human cells, consequently inhibiting MERS-CoV infection [5]. Similarly, in SARS-CoV-2, nafamostat blocks viral entry by inhibiting membrane fusion between the outer membrane of the virus and human cells [4, 6, 7]. Nafamostat mesilate has anti-inflammatory effect by inhibition of the complement pathway and inhibition of cytokine production [8].

Our study contributes to the establishment of treatment strategy in patients with COVID-19 pneumonia by evaluating the therapeutic effect of nafamostat mesilate through comparing the improvement in severity and reduction in mortality between the nafamostat mesylate with standard therapy group and standard therapy only group.

## Objectives {7}

### Research hypothesis

The main hypothesis of this study is that it shows a rapid recovery from symptoms and viral suppression in the intervention group.

## Study objective

### Primary objective

The primary outcome of this study will be to evaluate the proportion of patients with clinical improvement as defined by live discharge from hospital or a decline of 2 categories on the seven-category ordinal scale of clinical status.

### Secondary objective

Secondary objective comprised change in National Early Warning Score, duration of hospitalization, incidence of new-non-invasive ventilation or high flow oxygen use or ventilator, mortality at day 28, viral load change, and adverse events.

## Trial design {8}

The trial is designed as a randomized, open labeled, multicenter, two-arm with 1:1 allocation clinical trial in South Korea. This study compares the effect of nafamostat mesylate injection with standard treatment on 42 patients with COVID-19 pneumonia in the intervention group versus 42 patients with COVID-19 pneumonia with standard treatment only in the control group.

## Methods: participants, interventions, and outcomes

### Study setting {9}

This study is a multicenter trial conducted at 10 hospitals in South Korea to generalize the results, and 10 hospitals are located in various cities.

## Eligibility criteria {10}

### Inclusion criteria

18 years old or olderPatients who have been confirmed of COVID-19 infection and has evidence for pneumonia
A.Confirmation of COVID-19 infection by RT-PCR of SARS-CoV-2B.Definite diagnosis of new infiltration of the lungs by chest CT scan of chest radiographic inspection3.Patients who are within 72 h of COVID-19 pneumonia confirmation4.Patients with 3 (hospitalization, not requiring supplemental oxygen) or higher in seven-category ordinal scale of clinical status5.Patients who are eligible for diagnosis/evaluation to chest CT scan and related to it6.Patients should be able to understand the essence of the clinical trial and to submit a written consent document. For the patients who can understand the nature of the research but cannot sign the document, a relative can agree to the study.

### Exclusion criteria

Patients who have a record of HIV or AIDSFemale patients, either who are pregnant within 6 months before the investigation, who breastfed babies within 3 months before the investigation, or who may get pregnant or breast-feed within 1 month after the investigation is overPatients at high risk of death within 3 days of randomized assignment, by the judge of the investigatorPatients with liver cirrhosis with Child-Puch score being B or CPatients who have liver disease abnormalities with ALT or AST > 5 times ULNPatients who can be in danger or who shows clinically important other conditions which may interfere with the evaluation or completion of the test procedure, as the investigator’s opinionPatients who are not appropriate for the test, as the investigator’s opinionPatients who have hypersensitivity to the investigational drug

## Who will take informed consent? {26a}

The principal investigator or assistant researcher with trained research nurse in each hospital explains the purpose, potential benefits, and risks of the study and the right to refuse to participate or withdraw consent at any time and will obtain written consent from patients willing to participate in the trial. Copies of the consent document are provided for all patients involved in the study.

## Additional consent provisions for collection and use of participant data and biological specimens {26b}

Additional biological samples will be obtained to be stored for use in future studies of the pathobiology of COVID-19. A materials consent will be obtained to specifically address the collection of urine, serum, and plasma specimens.

The data collection/request is covered in the original informed consent process for the COVID-19 trial, and a separate consent form for research/donation of human materials administered by the Gyeongsang National University Hospital Institutional Review Board is also received.

Participants will be informed that their withdrawal from the ancillary research is possible.

## Interventions

### Explanation for the choice of comparators {6b}

There is no proven treatment for COVID-19 patients yet, and the standard treatment group is justified as it contains drugs and treatments known to be effective for COVID-19 patients to date. Drugs found to be effective in patients with COVID-19 will be added to standard treatment by protocol modification.

### Intervention description {11a}

Eligible patients will be randomized in equal proportions between standard treatment with nafamostat mesylate and standard treatment only.

Experimental group: nafamostat mesylate plus symptomatic treatment and lopinavir/ritonavir, hydroxychloroquine, antibiotics, non-invasive and invasive ventilation, renal replacement therapy (e.g., CRRT, HD), and ECMO as needed

*Nafamostat injection
Dosage: the researcher administers a dose of 0.1 to 0.2 mg/kg/h (2.4 to 4.8 mg/kg/day), taking into account the severity and underlying disease of the clinical trial patient.Method of administration: nafamostat injection is mixed with 1000 ml of 5% DW infusion, followed by continuous infusion over 24 h.Duration of administration: the researcher administers for 10–14 days considering the severity and underlying disease of the clinical trial patient.

Control group: symptomatic treatment and lopinavir/ritonavir, hydroxychloroquine, antibiotics, non-invasive and invasive ventilation, renal replacement therapy (e.g., CRRT, HD), and ECMO as needed

### Criteria for discontinuing or modifying allocated interventions {11b}

Suspension of administration: If the following serious adverse reaction occurs during the administration of the test drug, administration shall be stopped immediately.
Symptoms of shock or anaphylaxisSevere hyperkalemia: when there is a change in the electrocardiogram due to hyperkalemia or when the potassium blood concentration is above 7.0 mEq/LSevere hyponatremia: sodium blood concentrations below 120 mEq/L

### Strategies to improve adherence to interventions {11c}

Since the intervention protocol is performed during hospitalization, no adherence reminder is required beyond confirmation of discomfort associated with injectable medications. At the follow-up visit, the participant will be asked questions about any problems encountered after administration of the study medication.

### Relevant concomitant care permitted or prohibited during the trial {11d}

There are no contraindications to use in combination with the permission of the test drug.

### Provisions for post-trial care {30}

The Gyeongsang National University Hospital has insurance to cover for non-negligent harm associated with the protocol. This will include cover for compensation or damages whether awarded voluntarily by the Sponsor or by claims pursued through the courts. Incidences judged to arise from negligence (including those due to major protocol violations) will not be covered by study insurance policies. The liability of the manufacturer of nafamostat mesylate is strictly limited to those claims arising from faulty manufacturing of the commercial product and not to any aspects of the conduct of the study.

When a patient enrolled in the study has discharged, the clinical research coordinator contacts the participants to check for occurring side effects after discharge and provide information on the outpatient follow-up schedule. During outpatient visit including blood tests, adverse events are checked.

## Outcomes {12}

### Primary outcome

The primary outcome is as follows: proportion of patients with clinical improvement as defined by live discharge from hospital or a decline of 2 categories on the seven-category ordinal scale of clinical status [time frame: day 14 and day 28]

*Seven-category ordinal scale of clinical status
Not hospitalized with resumption of normal activities;Not hospitalized, but unable to resume normal activities;Hospitalization, not requiring supplemental oxygen;Hospitalization, requiring supplemental oxygen;Hospitalization, requiring nasal high-flow oxygen therapy and/or noninvasive mechanical ventilation;Hospitalization, requiring extracorporeal membrane oxygenation and/or invasive mechanical ventilation;Death.

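### For patients entering in category 3 or 4, clinical improvement means leaving hospital, while only the nafamostat arm has a 10–14 day inpatient infusion: time to improvement, hospital stay and day-7 status are tilted against nafamostat

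*Protocol article*

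**What the plan says.** Under Outcomes {12}, the primary outcome is the proportion with "clinical improvement as defined by live discharge from hospital or a decline of 2 categories" on the seven-category scale, with "time frame: day 14 and day 28" and no stated priority between the two days. The scale begins with two categories outside hospital: "Not hospitalized with resumption of normal activities;Not hospitalized, but unable to resume normal activities". The next two are inpatient categories: "Hospitalization, not requiring supplemental oxygen;Hospitalization, requiring supplemental oxygen". The inclusion criteria admit "Patients with 3 (hospitalization, not requiring supplemental oxygen) or higher in seven-category ordinal scale of clinical status", so categories 3 and 4 are eligible at entry.

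Intervention description {11a} gives nafamostat by intravenous mixture, "followed by continuous infusion over 24 h", and "the researcher administers for 10–14 days considering the severity and underlying disease of the clinical trial patient". The control arm receives the same background care as needed, with no minimum course. The adherence section {11c} explains why no reminders are needed: "Since the intervention protocol is performed during hospitalization". The listed grounds for suspending the drug {11b} are serious reactions; recovery is not among them.

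The secondary outcomes include time to clinical improvement (the same event, counted from randomization), clinical status on days 7, 14 and 28, and duration of hospitalization. Time to improvement is analysed to day 28 by Kaplan–Meier and log-rank, and the main analysis is by intention to treat.

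**The concern.** One arm has a treatment course that keeps the patient in hospital, and the event being counted is, for many eligible patients, departure from hospital. A category 3 or 4 patient on nafamostat who recovers on day 6 and is treated as written cannot be counted as improved until the infusion ends. An identical control patient can be counted on day 6. The constraint can delay the event in one arm and cannot bring it forward in either, so its direction is known.

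The research hypothesis is about rapid recovery, so the distortion falls on the outcomes that measure speed. Those outcomes could make an inert drug look harmful or hide a real benefit, because they partly measure the infusion schedule.

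**Working it through.** **Step 1: the scale.** Subtract two categories from each eligible baseline category.

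| Baseline | After a 2-category fall | Where |
|---|---|---|
| 3 | 1 | out of hospital |
| 4 | 2 | out of hospital |
| 5 | 3 | in hospital |
| 6 | 4 | in hospital |

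For baseline 3 and 4, both limbs of the definition amount to leaving hospital. Patients in categories 5 and 6 can improve as inpatients and are not held back by this route.

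**Step 2: timing.** Let T be the time at which a patient is fit for discharge and L the end of the infusion. In the control arm the event occurs at T. In a category 3–4 nafamostat patient treated as written it occurs at max(T, L), with L about 10 to 14 days. On day 7 no such patient can score 1 or 2.

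**Step 3: size.** The plan gives no figure on this point, so there is none to reproduce. From the document come 42 patients per arm, L of 10–14 days, and the assumed control rate of 80%, taken here as the day-28 rate (the document does not say which day it refers to). The recovery curves and the share of patients in categories 3–4 are assumptions. Both arms have the same T, that is, no drug effect.

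*Extra stay* per affected patient is E[max(L − T, 0)].
- Exponential T with 80% by day 28: λ = ln 5 / 28 = 0.0575. Extra stay = L − (1 − e^(−λL))/λ. For L = 10: 10 − 0.437/0.0575 = 2.4 days. For L = 14: 14 − 0.553/0.0575 = 4.4 days.
- Lognormal T with median m and log-SD 0.5: extra stay = LΦ(d) − m·e^0.125·Φ(d − 0.5), where d = ln(L/m)/0.5. For m = 7, L = 14: d = 1.386, giving 14 × 0.917 − 7.93 × 0.812 = 6.4 days (5.9 with times in whole days). For m = 14, L = 10: d = −0.673, giving 10 × 0.250 − 15.86 × 0.120 = 0.6 days, or 0.3 averaged over the arm if half are affected.

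*Log-rank on time to improvement*, simulated with 42 per arm: share of trials with z < −1.96 (nominal 2.5%).
- Exponential, all patients affected: about 15% with L = 10, about 40% with L = 14.
- Weibull with shape 1.8 (slower early recovery) and L spread over 10–14: about 5% with all affected, about 3% with 70% affected.
- Lognormal with median 10 days, all affected, L = 14: 93%. This curve has 98% recovered by day 28, well above the planned 80%.

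*Day-14 improvement.* With L at or before day 14 and discharge on the last infusion day, the difference is 0. For a fixed 14-day infusion under the exponential curve it is 0 if a day-14 discharge counts. If it does not count, the difference is −(1 − e^(−0.0575×14)) = −55 points. With whole-day infusions of 10 to 14 days in equal shares and discharge the day after, one patient in five is lost: 92% × 0.8 = about 73% (median 7) or 50% × 0.8 = 40% (median 14).

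*Day-28 improvement* is the same in both arms in every run, because all infusions have ended.

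**The case against.** The strongest reply has five parts.

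- **Early discharge is not shown to be barred.** The withdrawal section lets the investigator end participation at any time, for reasons beyond those listed, and premature discontinuation of treatment is a safety outcome. The adherence section says treatment is given in hospital; it does not say that stay is prolonged to complete it. This stands, and it is why the point is limited to patients treated as written. Early discharge would, however, cut short the stated 10–14 day course, so the sections still pull against each other.
- **Day 14 may be untouched.** A reader might infer that the day-14 primary reading is biased throughout, by as much as 55 points. The document does not support that. Duration is set individually, and the 55 points need every patient to be in category 3–4, to receive a full 14-day infusion, and to have a day-14 discharge not counted.
- **The size is driven by assumptions.** The article gives no baseline category mix, discharge criteria or usual time to discharge. If control patients also stay past day 14, little bias remains. This stands.
- **Other outcomes do not need discharge.** Time to NEWS of 2 or less held for 24 hours, NEWS change, and the oxygen and ventilation outcomes are already planned. This stands and shapes the fix.
- **The bias is conservative.** It cannot create a false claim of efficacy. Replacing actual discharge with a clinician's fit-for-discharge date, judged open label, could introduce bias in nafamostat's favour. This also stands.

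**Conclusion.** The structural point holds on the text alone. For category 3–4 patients treated as written, time to clinical improvement, duration of hospitalization and day-7 clinical status are biased against nafamostat. Day 14 is affected only where infusions run through that day and discharge follows; day 28 is essentially unaffected.

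The size is undetermined. Under no drug effect, the assumed curves give a stay about 0.3 to 6 days longer on nafamostat. With curves anchored at 80% by day 28, a log-rank result significantly against nafamostat occurs in about 3% of trials (slow early recovery, 70% affected) to about 40% (exponential, all affected, 14-day infusion). The 40% is not a ceiling: faster and more concentrated recovery gives more, as the 93% case shows.

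A reader might go further and infer that the primary analysis as a whole is invalid. It is not: day 28 is already a primary time point and is sound in this respect. This should be put right before analysis, but it does not undermine the trial.

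**What to change.** - Name day 28 as the single primary time point and make day 14 secondary.
- State that time to clinical improvement and duration of hospitalization include the stay imposed by the infusion in the nafamostat arm, and that day-7 status (and day-14 status where infusions are still running) is read with that in mind.
- Interpret speed of recovery with outcomes already planned that do not need discharge: time to NEWS of 2 or less maintained for 24 hours, and duration of oxygen use.
- Optionally, record in both arms the date on which the patient was fit for discharge apart from completing study infusion. Use it only in a sensitivity analysis, because it is an unblinded judgement.
- Reconcile the intervention description {11a}, the adherence section {11c} and the primary and secondary outcome definitions {12}. No infusion duration or stopping rule is proposed here.

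The cost is some wording, the loss of primary status for day 14 and, if the optional date is adopted, one extra eCRF field.

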### Sample size {14}

The sample size was calculated based on the assumption that superiority test (nafamostat treatment is right) of the treatment effect (effect size 10%) between two treatment groups (control group vs. nafamostat-treated group) will be carried out. The superiority margin is set to 0.05 (5%) based on the assumption that the nafamostat-treated group shows higher effect (90.0%) over the control group (80.0%). Nafamostat will be concluded as effective when the nafamostat-treated group shows 5% of higher effect compared to the treatment rate of the control group (80%). A one-sided significance level of 0.05 and power of 80% with equal allocation to two arms would require 42 patients in each arm of the trial.

Basic parameters for the sample size calculation are as follows:
Significance level, alpha = 0.05 (one-sided test)Power = 70%/80%/90%The ratio of the control group and the experimental group (nafamostat treatment) patients is 1:1Cure rate of the control group: 80%The cure rate of the experimental group (nafamostat treatment): 90%Superiority margin: 5%Expected drop out proportion: 5% (control, experimental each)

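### The primary outcome is set at both day 14 and day 28, but the single alpha, planning rates and success rule name no day, so the deciding result is undefined

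*Protocol article*

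**What the plan says.** The Primary outcome section under Outcomes {12} describes one outcome, a proportion improved, and attaches two days to it: "a decline of 2 categories on the seven-category ordinal scale of clinical status [time frame: day 14 and day 28". It does not say whether improvement is judged by each day or at each day.

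The rest of the article treats the primary comparison as single:

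- The Primary objective is to evaluate "the proportion of patients with clinical improvement as defined by live discharge from hospital" or a two-category decline, with no day. The Abstract gives none either.
- Sample size {14} sets "Significance level, alpha = 0.05 (one-sided test" and concludes that "A one-sided significance level of 0.05 and power of 80% with equal allocation to two arms would require 42 patients in each arm". It lists one control rate (80%) and one experimental rate ("The cure rate of the experimental group (nafamostat treatment): 90"%), neither with a day.
- The same section has one rule for concluding that the drug is effective, based on a 5-point margin ("Superiority margin: 5"%), again with no day.
- Statistical methods {20a} assigns Pearson's chi-square test to categorical variables in general. It mentions day 14 only for virus removal and day 28 only for time to clinical improvement, both secondary outcomes.

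Nowhere does the article say which day decides, or whether both must succeed.

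**The concern.** A proportion read on two days gives two test results, and the success rule in Sample size {14} cannot be applied until one is chosen or a way of combining them is stated. If the days agree, nothing is lost. If only one is significant, the protocol supports a positive and a negative conclusion equally well.

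Two things are at stake. The first is the false-positive rate: if the more favourable day may be called primary, the one-sided 5% is exceeded. The second is power: if both days must succeed, a sample size planned for one comparison is too small for the joint requirement. The trial is open label and the treating side rates the ordinal scale, so a choice of day left open is more exposed than usual to being made after results are seen.

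**Working it through.** **The plan's own figure.** Inputs from Sample size {14}: one-sided alpha 0.05, power 80%, 80% v 90%, margin 5 points, dropout 5% per arm; 1:1 allocation from Trial design {8}. With unpooled variance, n = (1.645 + 0.842)² × (0.80×0.20 + 0.90×0.10) / d².

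- d = 0.10 − 0.05 = 0.05 (margin applied): 619 per arm, 652 after dropout.
- d = 0.10 (no margin): 155 per arm, 164 after dropout.
- d = 0.20, which the article does not state: 39 per arm, 42 after dropout.

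The stated 42 is not reproduced from the stated inputs. That is a separate fault, and the present point does not depend on it. What matters here is that the calculation is for one comparison only.

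**Either day counts.** Assume improvement is judged by each day, so that anyone improved by day 14 is also improved by day 28 (nested outcomes). Under no effect the two test statistics then correlate as

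ρ = √[ p14(1 − p28) / (p28(1 − p14)) ],

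and the chance of at least one false positive is 1 − P(Z14 < 1.645 and Z28 < 1.645), with the pair bivariate normal. Each day is tested at one-sided 0.05 without a margin. The chance that both are significant is 0.05 + 0.05 minus the either-day figure.

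*Case A: 80% placed at day 28, day-14 rate assumed.* For example, p14 = 0.40 gives ρ = √(0.40×0.20 / (0.80×0.60)) = 0.41.

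| p14 (assumed) | p28 | ρ | Either day | Both days |
|---|---|---|---|---|
| 0.40 | 0.80 | 0.41 | 9.0% | 1.0% |
| 0.55 | 0.80 | 0.55 | 8.6% | 1.4% |
| 0.65 | 0.80 | 0.68 | 8.1% | 1.9% |
| 0.70 | 0.80 | 0.76 | 7.7% | 2.3% |

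A simulation at 42 per arm (400,000 trials per setting, pooled z test) gave 9.1% at p14 = 0.40 and 7.9% at 0.70 for either day, and 1.0% to 2.3% for both. Each single day rejected in about 5% of trials.

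*Case B: 80% placed at day 14, day-28 rate assumed.*

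| p14 | p28 (assumed) | ρ | Either day | Both days |
|---|---|---|---|---|
| 0.80 | 0.82 | 0.94 | 6.4% | 3.6% |
| 0.80 | 0.95 | 0.46 | 8.9% | 1.1% |

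The upper bound, for independent results, is 1 − 0.95² = 9.75%. It is not a realistic value, because the two results are positively correlated.

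**With the 5-point margin.** If each day must exceed the margin, a drug with no effect has to pass 1.645 + 0.05/SE. At 42 per arm and p28 = 0.80, SE = √(2×0.16/42) = 0.087, the threshold is 2.22 and the day-28 error is 1.3%. At day 14 (p14 0.40 to 0.70) the threshold is 2.11 to 2.15 and the error 1.7% to 1.6%. Either day passes in about 2.9% down to 2.4% of trials. With a margin test, the 7.7-9.0% applies only to a drug whose true advantage equals the margin on both days.

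**Both days required.** The error stays below 5%, as the last columns show. Joint power cannot exceed power on the weaker day. For 80% v 90% at 42 per arm, single-day power is already only about 36% without the margin and 16% with it.

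**The case against.** The strongest objection is that no passage states an either-day rule. Setting an outcome at day 14 and day 28 can mean that both must succeed, or that one outcome is reported at two visits. A reader might infer that the plan grants two chances of success and that the 5% error rate therefore fails. The documents do not support that as a statement of fact. The inflation is conditional on a rule that the article neither adopts nor excludes, and a both-days rule would give no inflation. This part of the objection stands.

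It is also fair that testing order and alpha sharing are commonly left to the SAP, which is not shown. Their absence is not charged here. The time point, however, belongs to the definition of the outcome, and the article does fix it, with two values set against one alpha and one pair of rates.

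The assumptions behind the figures also deserve challenge. The day-14 rates are not in the documents. Placing the 80% at day 28 is a choice, and Case B shows the effect of the alternative. Nesting fails if status is read at each day and patients can relapse. Under the margin, a drug with no effect passes less than 5% of the time. All of this limits the figures; none of it supplies the missing day.

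A reader might also suppose that the two days are likely to disagree because some patients are still on infusion near day 14. The documents do not show this. Administration runs 10-14 days, and the calculated correlations reach 0.76 in Case A.

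**Conclusion.** The point holds in conditional form. The protocol gives its primary outcome two time points and plans, powers and judges the trial as if there were one, so the deciding result is not defined.

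Whether the type I error is inflated depends on the rule adopted:

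- Either day, no margin, one-sided 0.05 each: about 7.7-9.0% under Case A, 6.4-8.9% under Case B.
- Both days: about 1.0-2.3% under Case A, with reduced power and a sample size that does not cover the requirement.
- Either day, 5-point margin, drug with no effect: about 2.4-2.9% under Case A.

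These figures rest on nested outcomes, the normal approximation and assumed rates for the day to which the 80% is not assigned. The ambiguity itself rests on no assumption: under each of these readings the plan needs a rule that it lacks. It also does not follow that day 28 is the only valid choice; nothing in the article shows to which day the 80% and 90% belong.

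**What to change.** Name one day as the single primary time point, and say whether improvement is judged by or at that day. Day 28 is a reasonable choice, because time to clinical improvement and mortality already use 28 days of follow-up. Carry the day into the Primary objective, the success rule and the analysis section.

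State which day the 80% and 90% planning rates refer to. If they were not meant for the chosen day, give rates for that day and redo the sample size.

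Make the other day a key secondary outcome, tested only if the primary succeeds. This fixed sequence keeps the error at 5% and needs no extra patients. A sequence in the other order, a both-days rule or an alpha split would also resolve the ambiguity, but the last two cost power: at 0.025 per day, the no-margin sample size for 80% v 90% (pooled variance) rises from 157 to 199 per arm before dropout.

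The trial is open label and the first patient enrolled on 7 July 2020, so record the date of the decision and that it was made without sight of outcome data compared by arm.

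The cost is a change of wording in the protocol, registry entry and SAP. The schedule already collects the ordinal scale on both days. The downside is that no stand-alone primary claim can be made on the other day.
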